#### **b. Missing data and drop-outs**

Some individuals will fail to complete all questionnaires. GLMM is designed to handle this type of missing data and will give unbiased estimates of intervention effects provided that the probability of having missing data depends only on the covariates in the model. We will check this assumption by looking at predictors of missing data. We will also run analyses to examine whether study participants who drop out of the study differ from those who do not. We will examine the data with complete case analyses (intent to treat). With the use of GLMM, we will be able to include all participants in the analysis, even those with missing values for some time points and those who drop out early. Everyone who begins their intended treatment is considered to be part of the trial whether they finish it or not. The methods of GLMM in effect estimates missing values, but we will also use alternative multiple imputation methods to estimate missing values using differing assumptions if the data appear to not be missing at random.

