## **C. Approach**

### **C.1 Overview and Design**

The primary purpose of this trial is to investigate whether true acupuncture is more effective than sham acupuncture or standard care for preventing radiation-induced xerostomia. Prior to radiation therapy, patients will be randomized into three groups: G1 (n=100) will receive true acupuncture, G2 (n=100) will receive sham acupuncture, and G3 (n=100) will receive standard care. Patients in the acupuncture treatment groups will receive up to 21 treatments over the course of radiotherapy with no more than 3 treatments per week. The duration of acupuncture therapy in the proposed study is the same as in our pilot trials. It has been shown to have a good effect in our phase II trial and small placebo controlled trial conducted at Fudan Cancer Hospital. Furthermore, inconvenience is minimized for participants because acupuncture is provided on the same day as radiation therapy.

Potential study participants will be identified by faculty in the departments of Radiation Oncology at Fudan Cancer Hospital and M. D. Anderson and referred to the research nurse for assessment of eligibility and informed consent counseling. Potentially eligible patients will be contacted in person when they are in the clinic so that the research nurse can describe the study in detail, answer the patients' questions, and assess their interest in the study. Approximately half the patients will be recruited from each center (193 patients at MD Anderson and 242 at Fudan) for a total sample size of 435 patients (see Appendix D. Study Schema, Study Schedule, Study Timeline).

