Patients will be randomized by a form of adaptive randomization, called minimization, because simple randomization could result in covariate imbalances (63). Statistical adjustment of covariates can take imbalances into consideration, but results are generally more credible when they are obtained from groups with comparable baseline distributions. In minimization, group assignment is done sequentially. In this study, the patient characteristics used for group assignment will be stage of disease, age (running mean), sex, the mean planned parotid doses (left and right side will be calculated separately and balanced between groups; <10, 10-<20, 20-<26, 26-<30, 30-<35, 35-<40, 40-<50, 50-<60, ≥60), induction therapy (yes/no), and concurrent chemotherapy (yes/no). Randomization will be conducted at each site separately. This will ensure equal distribution of all factors across all groups and balanced at each site. Information on group assignment will be only communicated to the acupuncturists by the data managers to insure that the research staff remains blinded.

Treatment will be withheld if lab values are not within an acceptable range (ANC>500; platelet count>20K/ml; INR, 3.0); if the study participant is diagnosed with a mental incapacitation or significant emotional or psychiatric disorder that interferes with his/her ability to cooperate with study procedures; or if a participant receives any heparin or warfarin during the treatment period.

Participants will be dropped from the study, at any point during the study, if the participant begins taking a prohibited medication (Appendix F) or if the participant encounters a cerebrovascular accident or spinal cord injury.

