#### **c. Usual care**

Participants in G3 will receive standard care. This will include being provided with standard oral care recommendations. Participants in all groups will receive the same recommendations.

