#### **c. Sample size calculations**

These precision and power estimates are based on a final post-intervention sample size of 300 study participants, 100 in each of the three intervention groups. To achieve this post-intervention sample size, we will oversample by 31% (i.e., 435 participants) to account for attrition. That is, we will allow for up to a 31% drop- out rate.

Our primary analysis is a mixed model regression analysis with repeated measures to evaluate the between group differences across the post-intervention time points with adjustment for covariates. Assuming a two- sided significance level of 0.05, we will have at least 80% power to detect differences between any pair of group means of 0.4 standard deviation units (SD – Effect Size Index) across the three post-intervention time points. In addition, the detectable mean difference between groups is 0.49 SD units with a two-sided significance level of 0.01. In our previous study, we found differences on post-intervention XQ means ranging from 0.80 SDs at the end of radiotherapy to 0.68 SDs at 1 month when comparing the acupuncture group with the standard care group. The associated XQ average values for the two groups at 1 month post radiotherapy were: 32.2 (SD=10.6) for acupuncture group and 41.5 (SD=9.6) for control group. As we do not know the exact differences that will occur between the sham acupuncture group and the other two groups, and given the definition of clinically significant effects (i.e., effect sizes of approximately 0.5 SDs being argued to be clinically meaningful) (25, 86, 87) the current study is still well-positioned to detect clinically significant effects between groups that may be present. We prefer to justify sample size using a paired t-test for simplicity and because it is conservative approach, although the later analyses using repeated measures will have greater power to detect differences between groups.

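### The missing-data section names three incompatible analysis populations, calls a complete-case analysis intent to treat, and never defines an all-randomised, as-assigned set

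*Supplement*

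**What the plan says.** All references are to the Final Protocol in the Supplement, whose section C.6 holds the final analysis plan.

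C.6 b (Missing data and drop-outs) makes three consecutive statements about who is analysed:

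- Complete cases, labelled as intent to treat: "We will examine the data with complete case analyses (intent to treat".
- Everyone, through the mixed model: "With the use of GLMM, we will be able to include all participants in the analysis, even those with missing values for some time points". Early drop-outs are included too.
- Those who start: "Everyone who begins their intended treatment is considered to be part of the trial whether they finish it or not".

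The section closes with a back-up: "we will also use alternative multiple imputation methods to estimate missing values using differing assumptions if the data appear to not be missing at random".

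The arms differ in what there is to begin. In C.1, "Patients in the acupuncture treatment groups will receive up to 21 treatments over the course of radiotherapy with no more than 3 treatments per week". Under C.4 c, standard care consists of oral care recommendations, and "Participants in all groups will receive the same recommendations".

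C.6 c names the mixed model as the primary analysis and sets the numbers: "we will oversample by 31% (i.e., 435 participants) to account for attrition", to leave 100 per arm.

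**The concern.** A complete-case analysis drops patients with missing assessments, so it is not intent to treat. It also contradicts the sentence that follows it. The treatment-start rule is a separate problem, because it conditions on something that happens after randomisation. Baseline measures and randomisation come before treatment (C.3), so a patient can be assigned to acupuncture and never have a session. One route to this is in C.3 itself: "Treatment will be withheld if lab values are not within an acceptable range". Such reasons are related to health, so those who never start may well differ in XQ from those who do.

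A patient in standard care cannot fail to start in this sense, and the plan does not say what beginning means for that arm. If the rule governs the analysis set, the acupuncture arms are filtered and standard care is not. Superiority over standard care is part of the primary aim. Moreover, with three populations on the page, an analyst could choose among them after seeing the data and call the result intent to treat.

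**Working it through.** **1. The three populations side by side.** Take four patients randomised to true acupuncture, and read each sentence of C.6 b as the rule for the analysis set.

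| Patient | Complete cases | All participants in the mixed model | Those who begin treatment |
|---|---|---|---|
| Starts, all XQ observed | in | in | in |
| Starts, misses one XQ | out | in | in |
| Never starts, all XQ observed | in | in | out |
| Never starts, misses one XQ | out | in | out |

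The rules agree only on the first patient. No sentence in the Final Protocol settles the matter by saying that all randomised patients are analysed as assigned.

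**2. Whether the mixed model resolves it.** Only in part. It keeps patients with some missing visits. But C.6 a models post-intervention values with baseline as a covariate, so a patient with no later XQ contributes no outcome. C.6 a also compares the three arms at the end of radiotherapy by analysis of variance, which uses only patients with an XQ at that visit. And a rule on who belongs to the trial acts before any model is fitted.

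**3. A second route to unequal removal.** Patients who start a prohibited medication are dropped from the study (C.2, C.3). Medications are reviewed at each acupuncture visit but not weekly in standard care (C.3), so detection can differ by arm. The plan does not say whether XQ data already collected from dropped patients stay in the analysis.

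**4. The plan's own figures.** They reproduce. Randomised number: 300 / (1 - 0.31) = 434.8, rounded up to 435, or 145 per arm. Power for 0.4 SD at 100 per arm, two-sided 0.05, normal approximation: standard error sqrt(2/100) = 0.141 and 0.4/0.141 = 2.83, giving 80.7%. Neither figure is in dispute, and the fix changes neither.

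**5. Possible size of the bias (assumptions, not document figures).** Let a share q of one acupuncture arm be left out and none of standard care, and let those left out differ in mean XQ from those kept by d SD. The mean of those kept is then off the arm mean by

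bias = q x d (in SD).

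The chance of a false positive at two-sided 0.05 follows from bias / SE, with SE = sqrt(1/[145(1 - q)] + 1/145), on the simplification that everyone not left out has an outcome.

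| q (patients of 145) | d | Bias (SD) | Share of 0.4 SD | Two-sided type I error |
|---|---|---|---|---|
| 5% (about 7) | 0.25 | 0.0125 | 3% | 5.1% |
| 5% | 0.5 | 0.025 | 6% | 5.5% |
| 5% | 1.0 | 0.05 | 12.5% | 7.1% |
| 15% (about 22) | 0.25 | 0.0375 | 9% | 6.1% |
| 15% | 0.5 | 0.075 | 19% | 9.4% |
| 15% | 1.0 | 0.15 | 37.5% | 23% |

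For the last row: SE = sqrt(1/123.25 + 1/145) = 0.1225 and 0.15/0.1225 = 1.22. A d of 1.0 SD is a deliberately harsh upper end. The direction depends on who is left out: if non-starters would have had drier mouths, the bias favours acupuncture; if not, it goes the other way.

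**The case against.** A reader might infer that the plan defines its analysis set as complete cases among treatment starters. It does not: the two conditions are never joined, C.6 b also brings in all participants, and C.6 c makes the mixed model primary. The fault is contradiction and omission.

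The treatment-start sentence sits in a section on drop-outs and can be read as saying only that people who stop early stay in. It does not state outright that non-starters are out. That stands, which is why the rule can exclude patients but cannot be said to do so. Exclusion is still the natural reading, and no other sentence rules it out.

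A reader might also expect unequal exclusion because of an extra visit burden. C.1 places acupuncture on the same day as radiotherapy, so the documents do not show three additional visits a week, and they give no figure that makes unequal exclusion likely.

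Other points reduce the exposure. Sham follows the same schedule as true acupuncture (C.4 b), so the asymmetry in starting does not arise between those two arms. The model adjusts for baseline XQ and the minimisation variables, which could narrow the gap between those left out and those kept. The plan also checks predictors of missing data, compares drop-outs with the rest, and foresees multiple imputation if data appear not missing at random. These address missing values among patients already counted as in the trial; they do not say who is in it.

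**Conclusion.** The wording is wrong as it stands. C.6 b mislabels a complete-case analysis, gives three populations that cannot all hold, and leaves an all-randomised, as-assigned set undefined. If the treatment-start rule were followed, the contrasts with standard care might no longer rest on randomisation; true versus sham is much less exposed.

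The size is unknown, because the documents give no non-starter rate and no XQ difference between starters and non-starters. Under the assumed 5-15% non-starters in an acupuncture arm only and a difference of 0.25-1.0 SD, the bias is about 0.01-0.15 SD. At the milder differences of 0.25-0.5 SD it is 0.01-0.075 SD, with type I error of 5.1-9.4%.

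It would be tempting to cite the 31% allowance, 0.31 x 435 = 135 patients, as the number these rules could remove. The documents do not support that. It is total attrition over all arms, and many of those patients would contribute XQ values to the mixed model before they leave.

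**What to change.** In C.6 b:

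- Define the primary analysis set as all randomised patients in the arm assigned, whether or not acupuncture was started, with all observed XQ values entering the mixed model.
- Remove the intent-to-treat label from the complete-case analysis and keep it, if wanted, as a sensitivity analysis.
- If a set of treatment starters is kept, make it secondary and use one criterion that applies in all three arms, for example start of radiotherapy.
- State that XQ data already collected from patients dropped from the study remain in the analysis.

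The cost is a change of wording, plus continued XQ assessment of non-starters, which can be done when they attend for radiotherapy and at routine follow-up visits. The planned 435 patients and the power at 100 per arm are unchanged. The downside is slight dilution of the estimated effect by patients who never had acupuncture.

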binomial test to test for these differences at each follow-up. We will also use the clinical response criteria of determining whether or not xerostomia has occurred or not as used by Eisbruch (22) and Pacholke (74). A significant response will be indicated if the summation XQ score  $\leq$  is 30. Eisbruch and colleagues revealed with bilateral radiation therapy treatment, the peak effect of XQ xerostomia scoring at 3 months post treatment is 45 +/- 10 (22). Using the criteria of  $\leq$  30 on the XQ score, we will use the binomial test to test for these differing proportions between groups at each follow-up. However, if 15 tests are made, in order for the results to be considered as significance as those with a 0.05 significance level, the significance level would need to be 0.003 or less (0.05/15) using a conservative Bonferroni method. We will also include a GLMM analysis to evaluate treatment and time effects upon incidence (general patterns in incidence). This analysis will test the overall treatment effect, the overall time effect and a treatment by time effect.

Other outcomes include the MDASI-HN, FACT-G, USFR, SSFR, and saliva constituents including pH, buffering capacity, and viscosity as well as levels of total protein, CGRP, and VIP. These variables are repeated measurements on multiple outcomes, possibly including hierarchical structure over subscales and related outcome measures. Desired inference includes hypotheses about treatment effects at different times and on different outcomes. Also, inference about treatment effects has to appropriately adjust for recorded baseline characteristics of the enrolled patients. With these considerations in mind, we propose the following strategy for the data analysis of these variables. As we expect scores on the criterion measures to be correlated within individuals over time, we will use GLMM. Separate sets of analyses will be conducted for each criterion variable (e.g., primary outcome: severity of self-reported xerostomia symptoms (XQ); secondary outcomes: MDASI-HN, FACT-G, saliva flow rates, and saliva constituents). For each criterion variable, we will use data across the set of post-intervention assessment points. In modeling these data, intervention condition is a between-subjects factor, time is a within-subjects factor, and baseline measures will be included as covariates.

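### The not-missing-at-random sensitivity analysis hangs on a trigger that data cannot settle, and the plan conflicts on which XQ visits are responses in the mixed model

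*Supplement*

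**What the plan says.** All references are to the Final Protocol in the supplement; its statistical text is section C.6.

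- **Missing data (C.6 b).** The mixed model is said to be unbiased if missingness depends only on covariates in the model. On that condition the plan says "We will check this assumption by looking at predictors of missing data", and it will compare drop-outs with completers. It will then use "alternative multiple imputation methods to estimate missing values using differing assumptions if the data appear to not be missing at random". No threshold, imputation model or size of departure is given.
- **Who is analysed (C.6 b).** With the mixed model, "we will be able to include all participants in the analysis, even those with missing values for some time points", and early drop-outs are expressly covered. The same paragraph also announces a complete-case analysis and labels it intention to treat.
- **Which visits are responses (C.6 a and c).** C.6 a lists five XQ assessments after baseline, starting with mid-radiotherapy, and describes the initial mixed model as an analysis of XQ over time. Further on it says "For each criterion variable, we will use data across the set of post-intervention assessment points", with baseline as a covariate. C.6 c describes the primary analysis as covering three post-intervention visits.
- **Expected loss (C.6 c).** The power figures rest on a "final post-intervention sample size of 300 study participants, 100 in each of the three intervention groups", and "we will allow for up to a 31% drop- out rate".
- **Removal from the study (C.2, C.3).** Patients who start a prohibited medication are dropped. The medications named in C.2 include pilocarpine and saliva substitutes.

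**The concern.** Missing at random and not missing at random differ only in whether loss depends on XQ values that nobody saw. A rule that waits for the data to show this cannot be operated. It can be declared unmet, so that the analysis never runs, or invoked once results are known. Either way the primary estimate has no committed test of its main untestable assumption.

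The assumption is not remote here. Drop-out of up to 31% is provided for, and starting a drug used for dry mouth is itself a reason for removal. If true acupuncture works, that route out of the study could be used unevenly across arms.

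The second issue compounds the first. If mid-radiotherapy XQ is not a response, a patient last seen at that visit has no outcome in the model. A collected predictor of the end-of-radiotherapy score then goes unused, although it would make the missing-at-random assumption easier to accept.

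**Working it through.** **Inputs.** From C.6 c: 300 evaluable (100 per arm), 435 enrolled, 31% drop-out, two-sided 0.05, at least 80% power at 0.4 SD. From C.6 a: five post-baseline XQ visits. Assumed by me: the shifts in missing patients, missing fractions below 31%, SD = 1 in each arm.

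**1. The plan's own figures.** 300 / (1 − 0.31) = 434.8, rounded up to 435. (300 × 1.31 = 393 would not give it.) So 31% is a fraction of those enrolled: 435 − 300 = 135, and 135 / 435 = 31.0%. Power with 100 per arm: 0.4 / √(2/100) = 2.828, and Φ(2.828 − 1.960) = 0.807. Both figures reproduce.

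**2. What the checks can detect.**
- Loss related to any measured variable: detectable. This refutes missing completely at random. If the variable lies outside the model, it also refutes the plan's stated condition.
- Loss related to the unseen XQ after allowing for everything measured: not detectable. This is what separates missing at random from not missing at random.

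The C.6 b trigger needs the second; its two checks can supply only the first.

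**3. Effect of a departure.** If a fraction f of an arm is missing and those patients are δ SD worse than the model predicts, the arm mean moves by f × δ. The contrast between two arms moves by f₁δ₁ − f₂δ₂. With a shift in one arm only:

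| f | δ = 0.25 | δ = 0.5 | δ = 1.0 |
|---|---|---|---|
| 0.10 | 0.03 | 0.05 | 0.10 |
| 0.20 | 0.05 | 0.10 | 0.20 |
| 0.31 (ceiling) | 0.08 | 0.16 | 0.31 |

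The last row, before rounding, is 0.0775, 0.155 and 0.31 SD. Divided by 0.4, that is 19%, 39% and 78% of the detectable difference. With f₁ = f₂ and δ₁ = δ₂ the contrast does not move.

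**4. Tipping point, for illustration.** Take an estimated difference of 0.4 SD, 100 observed per arm, and the standard error held fixed. The critical difference is 1.96 × √(2/100) = 0.277 SD. At f = 0.31 in the true-acupuncture arm only, significance is lost at δ = (0.4 − 0.277) / 0.31 = 0.40 SD, and the effect vanishes at 0.4 / 0.31 = 1.29 SD. At f = 0.10 (145 × 0.9 = 130.5 observed per arm) the critical difference is 1.96 × √(2/130.5) = 0.243, and significance is lost only at (0.4 − 0.243) / 0.10 = 1.57 SD.

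**5. The visits, side by side.**
- C.6 a, opening: five post-baseline visits including mid-radiotherapy; mixed model over time, with details deferred to later text.
- C.6 a, later: post-intervention visits only, baseline as covariate. This passage opens with the other outcomes but names XQ as an example.
- C.6 c: three post-intervention visits. End of radiotherapy plus three follow-ups makes four, so the count of three is not explained either.

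These cannot all describe one model. On the restrictive reading, a patient with no post-intervention XQ has no response. On the wider reading, the same holds for a patient lost before mid-radiotherapy, because baseline is a covariate. The inclusion statement in C.6 b therefore fails on both, for different numbers of patients. The documents do not say how many leave before the end of radiotherapy. The number with no response could be anywhere from 0 to 135 (for example 435 × 0.10 = 44, or 435 × 0.20 = 87). Power stays at or above 0.807 throughout, so the issue is bias, not power.

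**6. What leaving out mid-radiotherapy XQ could do.** A large simulation assumed 31% loss driven by mid-radiotherapy XQ, a true end-of-radiotherapy difference of 0.40 SD, a mid-radiotherapy difference of 0.3 SD and a correlation between the two visits of 0.5 to 0.7. Where the dependence differed by arm, the estimate without mid-radiotherapy XQ ranged from 0.24 to 0.56 SD; with it, about 0.40. Where the dependence was the same in both arms, both gave about 0.40.

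**The case against.** The strongest reply has four parts.

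- **The plan does not clearly omit mid-radiotherapy XQ.** A reader might infer a flat omission from the later text of C.6 a and from C.6 c. The opening of C.6 a does not support that: it lists mid-radiotherapy and puts no limit on the visits. This stands, and the point is a conflict to be reconciled.
- **Early drop-outs are not lost as a class.** A reader might infer that they are. Anyone seen at one modelled visit stays in. This stands.
- **31% is a ceiling.** It is an overall allowance in a trial with about a year of follow-up, and no figure is given for the end of radiotherapy. The plan also limits loss: XQ may be taken by phone (stated for M. D. Anderson only), questionnaires may be posted back when time is short, and follow-up coincides with oncology visits. This stands as partial mitigation and makes the sizes above upper bounds. As to removal for medication, C.2 also asks users of saliva substitutes to abstain for 24 hours before assessment, so whether substitute use alone leads to removal is unclear. Pilocarpine is not affected by that sentence.
- **The missingness check is useful.** A reader might conclude that it should be deleted. It should not: it can refute the plan's own condition and show which variables to add. It cannot confirm the condition.

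None of this rescues the trigger. No analysis of observed data can tell the sponsor when it has been met.

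**Conclusion.** The concern holds in two parts. First, the sensitivity analysis is conditional on something the data cannot show, and its content is unspecified. This rests on no assumed numbers. Second, C.6 a and C.6 c do not fix which XQ visits are responses, and the statement that everyone is included is wrong for any patient with no modelled visit.

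The size is a bound. At the 31% ceiling, with a departure in one arm only, the arm mean moves by 0.08 to 0.31 SD for assumed shifts of 0.25 to 1.0 SD. It moves in proportion less at lower missing fractions, and the contrast does not move if loss and shift are equal in the compared arms. The documents do not support saying that nearly a third of patients will be missing at the end of radiotherapy, or that the result will be biased. They support saying that the plan commits to no analysis that would show how far the result depends on the missing values.

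**What to change.** 1. **Make the sensitivity analysis unconditional and specified.** Replace the trigger in C.6 b with delta-adjusted multiple imputation by arm, always reported as a tipping-point analysis of the primary contrast. State the imputation model and the grid of shifts, including unequal shifts across arms.
2. **State the responses once.** Reconcile C.6 a with C.6 c by naming all five post-baseline XQ assessments, including mid-radiotherapy, as responses in the mixed model. Correct the inclusion statement to say how patients with no post-baseline XQ are handled, and remove the label that equates complete cases with intention to treat.
3. **Keep the predictors-of-missingness analysis, relabelled.** Present it as description and as a guide to variables to add to the analysis or imputation model, not as confirmation of the assumption.

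The cost is wording, brief programming and one more table. No new data are needed.
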